### ***Load Progression***

In terms of load progression, participants will be asked to perform as many repetitions as they are able on their final set of each exercise. During weeks 1 – 6, if participants are able to complete 12 or more repetitions on their final set, participants will be required to increase the loads they are using to the next level. The final four weeks (weeks 7-10) of the training program, participants will be asked to complete as many repetitions as they are able on their final set. When they are able to complete 7 or more repetitions on their final set, they will be assigned to the next highest load on their progression chart for their subsequent workout. To facilitate proper load progression, four approaches will be employed by our research team. First, participants will be given a progression sheet that will guide them on what loads to use based upon their level of strength for any given exercise. During the first two study visits, this sheet will be reviewed to ensure understanding by the participants. Second, participants will be instructed to complete as many repetitions as they are able on their third and final set. This approach will allow for all participants to auto-regulate their load assignments and when they are able to complete one to two repetitions more than they are programmed to complete, they will be instructed to increase their load. Third, all study participants will be required to perform one workout per week under the direct supervision of a research team member. During this session, discussions surrounding exercise selection, load progression, etc. will be made to ensure participants understand and they are appropriately progressing the loads. Lastly, participants will be told to set a daily workout goal where their total volume-load (sets x repetitions completed x loads used) for each exercise should increase each week. Additionally, participants will be asked two compliance questions during each supervised workout: 1) are they following the load progression instructions as outlined, and 2) do they feel their unsupervised and supervised workouts are different in quality or intensity? These questions will allow for research team members to provide feedback and solutions to maximize consistency between workouts.

### ***Supervision & Compliance to Resistance Training Program***

Each resistance training session is anticipated to take approximately 60 minutes to complete. All supervised sessions will be performed between the hours of 0530-0800 hours, 1130-1300 hours, or 1600-2000 hours. Participants will be required to have a fitness staff attendant, personal trainer, strength and conditioning coach or workout partner sign off on completion of each workout. Further, study participants will be required to complete one weekly workout under the direct supervision of a research team member. If desired, participants can complete more supervised workouts per week, but a minimum of one weekly supervised workout will be required. For all unsupervised workouts, study participants must take a photograph of them in the gym with several pieces of exercise equipment in the background. No other human can be in the background of the photo. This photo

must be emailed directly [REDACTED] will be recorded for compliance.

### ***Dietary Protocol***

At the beginning of the study protocol, study participants will be provided dietary instruction from research team members on achieving and maintaining a daily diet that delivers appropriate calories and protein intake. A range of daily caloric needs will be estimated for each study participant by first calculating resting energy expenditure (REE) using both the Mifflin-St Joer and Cunningham equations. These values will be averaged and then this value will be multiplied by an activity factor of 1.55 and 1.75. In addition, study participants will be instructed to maintain a daily protein intake of 1.6 to 2.0 grams of protein per kilogram of body mass each day. Additionally, sample breakfast, lunch, dinner, and snack plans will be provided to all participants to assist them in meeting the calorie and protein intake guidelines for the study. Participants will be required to log their dietary intake over a 3-day period after 0, 2, 6, 8, and 10 weeks of following the supplementation program. For each dietary recall, participants will be asked to enter all of the food and fluid they consume onto a hand-written 3-day food log. Research team members will monitor and analyze all the energy and macronutrient intakes throughout the study and provide recommendations on any required changes if need be. Participants will be provided with instructions on how to properly estimate sample size and be given visual comparators to assist with accuracy of their food entries. If participants fail to meet the dietary recommendations for two consecutive weeks, they will be removed from the study.

### ***Supplementation Protocol***

After following the dietary protocol and resistance training program all individuals determined to be weight stable will be randomly assigned to ingest one daily dose in a double-blind fashion of 2 grams of dileucine (Ingenious Ingredients, Lewisville, TX), 2 grams of leucine (NNB Nutrition), or 2 grams of rice flour (placebo). Each dose will be mixed with approximately eight ounces of cold water. On workout days, participants will ingest their assigned dose within 60 minutes of completing their workout. On non-workout days, one dose will be ingested with their morning meal. Participants will be randomly matched according to DEXA fat-free mass for supplementation assignment.

### ***Adverse Event Reporting***

The occurrence of adverse events will be recorded throughout the entire duration of the study. When participants visit the laboratory during their weekly supervised workout, participants will report the frequency as well as the severity ('mild', 'moderate', 'severe') of any adverse event they report. In addition, adverse events will be collected through spontaneous reporting by the study participants, interaction of a research team member with a study participant, or through review of a study participant's compliance paperwork.

### **What forms or instruments will participants complete?**

---

*Attach all surveys, questionnaires, screening forms, or data instruments completed by participants (e.g. food diaries, reflection journals, follow-up surveys, etc...). If you are conducting interviews or focus groups, attach a list of applicable questions or prompts.*

*Note:*

- ***Do not attach Recruitment and Consent Materials, will be attached later in the application.***
- ***Qualtrics must be used for survey data collection, unless a prior exception has been granted by the IRB Office. (Register for Qualtrics [here.](#))***

[Diet Log-3-Day-Format.doc](#)

19.

[DTS RESISTANCE TRAINING HISTORY.docx](#)

[Health Fitness PreParticipation Screening Document.docx](#)

[Data Collection - Primary.docx](#)

[DTS Data Collection - Training Visit Data Log.doc](#)

[DTS Adverse Event Log.docx](#)

[EPNL Training Card.xlsx](#)

[Exercise Progression.xlsx](#)

[DTS Waiver of Documentation of Consent.docx](#)

[Participant Screening and Waiver of Documentation of Consent](#)

[ASA24](#)

\*required

20. **Will you provide compensation to participants?**

---

No

✓ Yes

\*required

## Describe your compensation plan:

---

*Note:*

- ***Include a description of the amount, timing, and type of compensation.***
- ***Describe who participants who withdraw will be treated. Will they receive full, partial, or no compensation?***

- 20a. Participants will receive monetary compensation (\$300) upon completion of all aspects of the study protocol. To process compensation requests, each participant will need to complete an internal document required for financial processing and a W9. To complete these forms, a participant will need to provide their name, social security number, employment status with Lindenwood University and mailing address. For non-employees of Lindenwood University, compensation will be made in the form of a check that will be made to an address specified by the participant. For Lindenwood University employees, the compensation will be added to their payroll and issued in the same form as how they are paid from Lindenwood University. All payments will be issued upon completion of participation and participants who do not complete the testing protocol may be eligible for a prorated amount of compensation commensurate with the proportion of the study protocol they complete, not to exceed 50% of the available compensation.

\*required

**Provide a rationale for how the compensation does not pose an undue influence to participants:**

---

- 20b. *An undue influence is an excessive or inappropriate reward, which may affect the voluntariness of a participant's consent and compliance.*
- Participants in this study will complete five separate visits. Visit 1-5 will only take approximately 1.5 hours. It is estimated that each participant will spend approximately 8 hours of actions directly related to the research study (talking on phone, getting ready for lab visits, driving to lab, completing lab visit) during their supervised training sessions. Participants are being compensated for time spent during the study, but the total compensation will not be enough to unduly influence a participant to complete the study against their personal judgment.

\*required

**Will your research involve any of the following?**

21. \_\_\_\_\_

*Check all that apply.*

Deception

✓ Investigational Drugs or Dietary Supplements

Investigational Devices

Retaining Data or Biological Samples for Future Research

None of the above

\*required

### Investigational Drugs or Dietary Supplements

---

*What drug, substance, or supplement are you investigating? Include:*

21c.

- *Information about the manufacturer*
- *The ingredients and formulation of the drug, substance, or supplement*
- *A description of any placebo and the constitution of placebo elements*

Leucine (2 grams), Dileucine (2 grams), Rice flower as placebo (2 grams)

\*required

### Investigational Drugs or Dietary Supplements

---

21d.

*Is this substance considered a "drug" by FDA? The [FDA definition of the term drug](#) includes, among other things, articles intended for use in the diagnosis, cure, mitigation, treatment, or prevention of disease, and articles (other than food) intended to affect the structure or any function of the body of man or other animals.*

✓ No

Yes

\*required

## **Investigational Drugs or Dietary Supplements**

---

### *How will you procure, label, handle, and store the drug or supplement?*

21e.

All dietary supplements will be procured according to the terms of the research agreement. All product will be provided in blinded, labeled containers prior to them arriving in the EPNL. Each beverage will be of a similar volume, texture, and flavor and labeled in indistinguishable bottles to ensure blinding. Upon handling all supplements, research team members will use personal protective equipment (gloves, jackets, eyewear, face mask) when handling all product. Prior to dispensing, the work area will be cleaned with a non-residue surface cleaner. Upon leaving the area, the research team member will discard gloves and use a fresh pair when commencing dispensing of the product.

\*required

## **Investigational Drugs or Dietary Supplements**

---

21f.

### *How will you dispose of any leftover substances?*

All leftover substances will remain in packaged containers and stored in a cool, dry, dark, and locked location until completion of all study activities. Upon completion, all leftover substances will be discarded with other dry chemicals.

\*required

### How many participants will you enroll?

---

22. *In most cases, provide a specific minimum number (e.g. 50) of participants to be enrolled. This can at times be a range with the upper limit identified, when it is unsure how many subjects may respond to a survey or how many subjects in a data set may be viable for analysis (e.g. 45-50).*

36

\*required

### What are the characteristics of your research population?

---

23. *These could include gender, age, ethnicity, race, health status, employment status, etc? If you are recruiting multiple populations, describe by population with anticipated enrollment by population.*

Approximately 36 healthy, resistance trained males between the ages of 18-35 are proposed to complete this study.

\*required

### What qualifies a participant for your research?

---

24. *Please include all inclusion criteria.*

- Male
- Between the ages of 18-35 years
- Currently participating in resistance training exercise

\*required

## What disqualifies a participant for your research?

---

*Please include all exclusion criteria.*

25.

- Female
- Participants who are determined to not be weight stable defined as week 0 and week 2 body mass levels deviating by 3% or more.
- Any individual who is currently being treated for or diagnosed with a cardiac, respiratory, circulatory, musculoskeletal, metabolic, immune, autoimmune, psychiatric, hematological, neurological or endocrinological disorder or disease.
- Body mass index  $> 25 \text{ kg/m}^2$ . Individuals with a body mass index greater than  $25 \text{ kg/m}^2$ , but a body fat percentage less than 25% fat will be accepted into the study
- Individuals who present with any previous injury or illness that would prevent them from appropriately completing all exercise lifts.
- Participants who are not able to fit onto the DEXA table will not be able to participate in the research due to size restrictions of the equipment. This typically includes individuals exceeding 400 pounds or those greater than 6'4".
- Those individuals with less than 12 months of structured resistance training experience will be excluded from the study.
- Individuals whose maximal relative upper body strength is below 1.0 will be excluded.
- Individuals whose maximal relative lower body strength is below 1.5 will be excluded.
- All participants who DO NOT abstain from taking any additional forms of nutritional supplementation deemed to be ergogenic or that will impact resistance training adaptations (pre-workouts, creatine, beta-alanine, etc.) for four weeks prior to beginning this study and for the entire duration of the study.
- Individuals who are currently using or have used within the past 12 months anabolic-androgenic steroids.

\*required

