In a randomized, double-blind, placebo-controlled fashion, participants will be matched according to their Visit 2 fat-free mass to ingest either two grams of dileucine, two grams of leucine, or a placebo (rice flour). All supplements will be provided by Ingenious Ingredients, L.P. (Lewisville, TX). On days where research participants will complete the exercise program, they will be required to consume their daily dose within 60 minutes of completing their workout. When the workout is completed at our facility, supplement ingestion will be monitored by a research team member. On non-training days, participants will consume their assigned dose with their morning meal. Participants will be given enough supplement for one week at a time as participants will be required to schedule and complete one workout per week under the direct supervision of a research team member. During these weekly workouts and check-in visits, participants will get more supplement, discuss their dietary compliance and ensure completion of their workout cards. Participants will continue to follow the prescribed resistance training program for the entire 10 weeks of the study protocol.

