#### Final Study Visit (Visit 5)

Approximately ten weeks after beginning the resistance training (40 workouts; a minimum of 36 required or 90% compliance) and supplementation protocol, study participants will report back to the lab for their final study visit during a similar time of day (0600 – 1000 hours). In an identical fashion as previously completed, participants will observe an overnight fast, ensure completion of all food and training records, return any remaining supplements and have their body mass, hydration, body water, body composition (DEXA), ultrasound, countermovement jump, maximal strength (bench

press 1RM, leg press 1RM, and isometric mid-thigh pull), muscular endurance (repetitions to failure using 80% [RTF] of their Visit 2 1RM for both exercises) and anaerobic capacity (WanT) determined. This visit is estimated to take 90 minutes to complete.

**Table 1:** Outline of testing for the 10-week study.

| Procedure                                     | Pre-Study
(Visit 1) | Week 0
(Visit 2)                                                                | Week 2
(Visit 3) | Week 6
(Visit 4) | Week 10
(Visit 5) |
|-----------------------------------------------|------------------------|------------------------------------------------------------------------------------|---------------------|---------------------|----------------------|
| Resistance Training Protocol                  |                        | [figure not shown] |                     |                     |                      |
| Supplementation Protocol                      |                        | [figure not shown] |                     |                     |                      |
| Review & Sign Consent                         | X                      |                                                                                    |                     |                     |                      |
| Screening (Health, Medical, Exercise History) | X                      |                                                                                    |                     |                     |                      |
| Height and Weight                             | X                      | X                                                                                  | X                   | X                   | X                    |

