| Heart Rate / Blood Pressure                   | X                      | X                                                                                  | X                   | X                   | X                    |
| Food Record*                                  | X                      | X                                                                                  | X                   | X                   | X                    |
| Randomization into Group                      | X                      |                                                                                    |                     |                     |                      |
| Body Composition                              |                        | X                                                                                  | X                   | X                   | X                    |
| One-Repetition Maximum (1RM)                  | X                      | X                                                                                  | X                   | X                   | X                    |
| Isometric Mid-Thigh Pull                      | X                      | X                                                                                  | X                   | X                   | X                    |
| Countermovement Jump                          | X                      | X                                                                                  | X                   | X                   | X                    |
| Muscular Endurance                            |                        | X                                                                                  | X                   | X                   | X                    |
| Anaerobic Capacity                            | X                      | X                                                                                  | X                   | X                   | X                    |
| Dietary Protocol*                             |                        | X                                                                                  | X                   | X                   | X                    |
| Resistance Training Program*                  |                        | X                                                                                  | X                   | X                   | X                    |

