## Procedures

### Body Mass

Body mass weight will be measured (Tanita BWB-627A, Tokyo, Japan) and recorded to the nearest  $\pm 0.1$  kg upon arrival at all study visits. The recorded body mass during visit 1 and visit 2 will be compared to ensure the participant is weight stable and any participant whose body mass changes by more than 3% during this time will be excluded from participation. In addition, body weight will be assessed to compare changes seen after completion of the supplementation and resistance training protocols.

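### The protocol gives conflicting rules on when weight stability is judged and when men are randomised; one version excludes randomised men on on-treatment body mass, and a separate diet rule removes randomised men from the study

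*Protocol*

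**What the plan says.** **Weight stability.** The exclusion criteria (question 25) rule out "Participants who are determined to not be weight stable defined as week 0 and week 2 body mass levels deviating by 3% or more". The Body Mass procedure instead compares Visit 1 with Visit 2 and states that "any participant whose body mass changes by more than 3% during this time will be excluded from participation". The Familiarization and Entry (Visit 1) section uses the same Visit 1 to Visit 2 comparison. Table 1 labels Visit 2 as Week 0 and Visit 3 as Week 2, so these are two different checks.

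**Randomisation.** Table 1 marks "Randomization into Group" in the pre-study (Visit 1) column. The Baseline Testing (Visit 2) section says that "participants will be matched according to their Visit 2 fat-free mass". The Supplementation Protocol says: "After following the dietary protocol and resistance training program all individuals determined to be weight stable will be randomly assigned".

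**Start of treatment.** Baseline Testing (Visit 2) has men begin both training and supplement at that visit. Question 14 and Experimental Design describe ten weeks of daily supplement, with testing after 2, 6 and 10 weeks on both regimens.

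**Removal.** The Dietary Protocol states: "If participants fail to meet the dietary recommendations for two consecutive weeks, they will be removed from the study". It schedules three-day food logs at Weeks 0, 2, 6, 8 and 10. Table 1 and its footnote mark the food record as weekly.

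**The concern.** Eligibility should be settled on information obtained before allocation. If a man can be excluded on something measured after he was randomised and began treatment, the groups compared are no longer the groups that randomisation formed. Body mass at Week 2 is an awkward variable for this purpose: fat-free mass is a primary endpoint and a large part of body mass, and training and supplement may both move it.

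Removal on diet has a different consequence. On its plain meaning, a man removed from the study does not return for later tests. No analysis plan can recover a Week 10 value that was never taken.

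There is also a practical problem. Staff following Table 1 would randomise at a visit where the matching variable has not been measured. Staff following the Supplementation Protocol would randomise at some later, unspecified point.

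**Working it through.** **1. The timeline as written.** Training is four sessions a week. 4 × 2 = 8 sessions by Visit 3 and 4 × 10 = 40 by Visit 5, which are the counts the protocol gives. Training therefore starts at Week 0, and Week 2 follows two weeks of it. For supplement, the sources differ:

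| Source | Implied start of supplement |
|---|---|
| Question 14; Experimental Design | Week 0 (ten weeks of supplement) |
| Baseline Testing (Visit 2) | Week 0 (both regimens begin) |
| Supplementation Protocol | After following diet and training |
| Specific Aims | Eight weeks of supplement; 10 − 2 = 8 would fit a Week 2 start |
| Statistical Analysis | Endpoint is Week 10 minus Week 2; would also fit a Week 2 start |

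The bars for training and supplement in Table 1 are graphics that I could not read. They must agree with whatever is decided.

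**2. The stability check against allocation.**

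| Rule | Window | Threshold | If supplement starts at Week 0 | If supplement starts at Week 2 |
|---|---|---|---|---|
| Exclusion criteria | Week 0 to Week 2 | 3% or more | After randomisation, on treatment | Could be a pre-randomisation screen |
| Body Mass; Visit 1 text | Visit 1 to Visit 2 | More than 3% (Body Mass) | Before treatment | Before treatment |

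The thresholds differ only at exactly 3%. For example, 80.0 kg to 82.4 kg is excluded under the first and kept under the second.

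**3. The Table 1 mark.** Body composition is first measured at Visit 2, both in Table 1 and in the Body Composition Assessment section. A randomisation at Visit 1 cannot be matched on Visit 2 fat-free mass, whichever start is intended.

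**4. Size of a Week 0 to Week 2 gate (illustration).** The protocol gives no mean or SD for early weight change, so these are assumed. Let the change be normal with mean m and SD s, in a man of assumed mass 80 kg. The limit is 0.03 × 80 = 2.4 kg.

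Share removed = Φ((−2.4 − m)/s) + 1 − Φ((2.4 − m)/s). The mean among those kept is that of the normal distribution truncated at ±2.4 kg.

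| m (kg) | s (kg) | Removed | Of 36 men | Mean among kept (kg) |
|---|---|---|---|---|
| 0 | 1.0 | 1.6% | 0.6 | 0.00 |
| 0.5 | 1.0 | 3.1% | 1.1 | 0.44 |
| 1.0 | 1.0 | 8.1% | 2.9 | 0.84 |
| 0 | 1.5 | 11.0% | 4.0 | 0.00 |
| 0.5 | 1.5 | 12.9% | 4.6 | 0.30 |
| 1.0 | 1.5 | 18.7% | 6.7 | 0.58 |

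With a smaller spread (mean 0%, SD 1% of body mass) the share is 2 × (1 − Φ(3)) = 0.3%, or 0.1 of 36 men. If one arm gained 1.0 kg on average and another 0 kg, the true 1.0 kg difference in early change would appear among the kept men as 0.84 kg (SD 1.0) or 0.58 kg (SD 1.5).

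**5. Loss of numbers (illustration).** With a normal approximation, two-sided α = 0.05 (sidedness assumed) and 80% power, the detectable pairwise difference in SD units is (1.960 + 0.842) × √(2/n). This gives 1.14 at n = 12 per arm, 1.25 at n = 10 and 1.40 at n = 8. The protocol states no power target for these to contradict.

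**The case against.** The strongest reply is that a two-week run-in was intended. The Supplementation Protocol assigns only men already found weight stable, the endpoint runs from Week 2, and the aims speak of eight weeks. On that reading the Week 0 to Week 2 check is an ordinary screen. This cannot be dismissed, and it is why the point is a contradiction and not a settled post-randomisation exclusion. It does not remove the problem: question 14, Experimental Design and Baseline Testing say otherwise, and Table 1 fits neither reading.

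It is also fair that the gate closes before the Week 10 minus Week 2 change begins. It does not truncate the primary outcome directly. It selects on a related variable, and Week 2 is the starting value of that change. Nothing in the protocol shows that removal would differ by arm.

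A reader might infer several stronger things that the document does not support:

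- **Men are removed for missing workouts.** The final-visit section sets "a minimum of 36 required or 90% compliance" (0.90 × 40 = 36) but attaches no consequence. Only diet has a removal rule.
- **The diet rule can never be triggered because no two consecutive weeks are observed.** Table 1 indicates weekly food records, and Baseline Testing describes weekly check-ins on diet. The defect is only that the two schedules differ.
- **The analysis will be completers only.** The protocol defines no analysis set, and a statistical analysis plan may do so.
- **Twelve per arm will not be delivered.** The enrolment answer is 36 and "Approximately 36 healthy, resistance trained males between the ages of 18-35 are proposed to complete this study", but that wording is approximate and replacement is not ruled out.

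**Conclusion.** The concern stands as an internal contradiction with a real consequence. The window and threshold for weight stability, and the timing of randomisation, cannot be followed as written. If supplement starts at Week 0, as most of the text says, the exclusion-list rule acts on randomised men after two weeks of treatment. The diet-removal rule raises a second problem that does not depend on how the weight rule is resolved: randomised men leave on post-baseline data, and their later outcomes would be lost.

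The size is unknown. The shares of 0.3% to 18.7% and the detectable differences of 1.14 to 1.40 SD rest on assumed means, SDs, body mass and losses. They show that the effect could run from negligible to material in a 36-man trial, not that it will be large.

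**What to change.** 1. Reconcile the exclusion criteria, the Body Mass procedure, the Visit 1 text, the Supplementation Protocol and Table 1 to one weight-stability window and one threshold, with the check closed before randomisation. The choice of threshold is the investigators'.
2. Move the Table 1 randomisation mark to after the fat-free mass measurement used for matching, and make the Supplementation Protocol agree.
3. If a two-week run-in was intended, say so, and align question 14, Experimental Design and Baseline Testing, including the visit that supplies the matching value. If not, align the aims' eight weeks and explain why the endpoint starts at Week 2.
4. State that randomised men who meet the diet-removal criterion are still invited to the remaining scheduled tests and are analysed in their assigned arm, with a secondary per-protocol set. Whether they continue supplement or training is for the investigators to decide.
5. Reconcile the Dietary Protocol's log schedule with the weekly records in Table 1, so that the two-consecutive-weeks criterion has one data source.

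The cost is amendment wording and a few test visits that are already in the schedule. The downside is some dilution of the treatment contrast by non-adherers, which the per-protocol set would help to show.
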